## 5.8 Assessing “Seriousness” and Serious Adverse Events

Seriousness refers to the outcome of an adverse event. Seriousness is determined by both the principal investigator and the local medical monitor. If either principal investigator or local medical monitor determines an event to be serious, it will be classified as such. If any of the following outcomes are present then the adverse event is serious:

- It results in **death** (i.e., the AE caused or led to the fatality). Serious does not describe an event which hypothetically might have caused death if it were more severe.
- It was immediately **life-threatening** (i.e., the AE placed the subject at immediate risk of dying. It does not refer to an event which hypothetically may have led to death if it were more severe).
- It required inpatient **hospitalization** or prolonged hospitalization beyond the expected length of stay. Hospitalizations for scheduled treatments and elective medical/surgical procedures related to a pre-existing condition that did not increase in severity or frequency following receipt of study vaccine, are **not** serious by this criterion. Hospitalization is defined as a hospital admission or an emergency room visit for a period greater than 24 hours.
- It resulted in a persistent or significant **disability/incapacity** (i.e., substantial reduction of the subject’s ability to carry out activities of daily living).
- It resulted in a **congenital anomaly or birth defect** (i.e., an adverse finding in a child or fetus of a subject exposed to the study vaccine prior to conception or during pregnancy).
- Other **medically important conditions** that may not result in death, threaten life or require hospitalization (i.e., the AE does not meet any of the above serious criteria) may be considered a serious adverse event when, based on appropriate medical judgment, they may jeopardize the subject and require medical or surgical intervention to prevent one of the serious outcomes listed in these criteria (e.g., allergic bronchospasm requiring intensive treatment in an emergency room or at home; blood dyscrasias or convulsions that do not result in hospitalization, or the development of drug dependency or drug abuse).

A **serious adverse event** is an adverse event meeting the outcome criteria for seriousness regardless of relationship to an administered medicinal product.

## 5.9 Assessing Expectedness

Expected adverse events are adverse events consistent with the applicable product information provided by the sponsor (the investigator’s brochure for an investigational product). The sponsor, in the person of the local medical monitor, determines expectedness. If the assessment is that the adverse event is **expected** no further action is required. If the local medical monitor’s assessment is that the adverse event is **unexpected**, then the event may represent a SUSAR (see Sections 5.10 and 5.11).

## 5.10 Definition of Suspected Unexpected Serious Adverse Reaction (SUSAR)

When an adverse event is judged to be related to an investigational product and also is judged to be serious and unexpected, it is a SUSAR (suspected unexpected serious adverse reaction) and is subject to expedited reporting.

## 5.11 Reporting of Serious Adverse Events

*Serious adverse events, which include SUSARs, are reported to the sponsor and to the World Wide Safety Center (administered by PPD, Inc.) for the entire study period (see protocol appendices). SUSARs are reported even after the trial is over, if the sponsor, local medical monitor or principal investigator become aware of them.* The site will be provided with specific reporting procedures including reporting forms to be used. Serious adverse events will be reported using a recognized medical term or diagnosis that accurately reflects the event.

Serious adverse events will be assessed by the investigator and the local medical monitor according to their roles (as described in Sections 5.1.2 and 5.1.4) for severity, causal relationship to the study vaccine, and expectedness. The onset and resolution dates of the event and the action taken in response to the event will be documented. If the event has not resolved by the final study visit, it will be documented as “ongoing” on the CRF, however, follow-up of the SAE must continue until resolved. Information recorded on the CRF must be substantiated in the source documents.

**An SAE Report completed for that event must be faxed or scanned and emailed by the principal investigator or his/her designee within 24 hours (one calendar day) of the investigative site becoming aware of the event to the local medical monitor, to the World Wide Safety Center and to the CRO, Triclinium . The SAE Report (paper form) should be completed and faxed (even if all information concerning the event is not yet known) within the first 24 hours of awareness of the event.**

**Fatal or life-threatening serious adverse events that the investigator suspects are related to the study vaccine should be telephoned to the local medical monitor immediately upon the investigator’s awareness of the event. If the local medical monitor is required by the protocol or chooses to suspend enrollment s/he shall immediately create a written memorandum for record to the study file and telephonically notify the sponsor of this act.**

**Contact information for all safety personnel are contained in the Team Contact List which will be stored on site in the Site Regulatory Binder and maintained by the study sponsor.**

Investigators must not wait to collect additional information to fully document the event before notifying the local and global medical monitors of a serious adverse event. The initial notification should include the following (at minimum):

- Protocol number and name and contact number of the investigator
- Subject ID number (and initials and date of birth, if available)

- Date subject received study vaccine
- Serious adverse event(s) and date of event onset
- Current status of subject

Aeras has authorized the PPD World Wide Safety Center to execute its responsibilities for safety report submission to the appropriate regulatory authorities within specific time periods of being notified of the event (within 7 or 15 calendar days depending the character of the SUSAR); therefore, it is important that the investigator submit additional information requested as soon as it becomes available. Triclinium will notify MCC; SATVI will notify UCT REC.

Aeras will notify the investigators at Oxford University and the Safety Monitoring Committee of all SAEs within three working days of becoming aware of an event and will provide all follow-up information in a timely manner.

### 5.12 Other Events Requiring Immediate Reporting

The investigator must report the following events by faxing the appropriate form to the local medical monitor and Triclinium within 24 hours of becoming aware of the event:

- Withdrawal of consent during the study (Immediately Reportable Event Form)
- Emergency unblinding (Immediately Reportable Event Form)
- Protocol violation affecting the safety of a subject or involving the vaccination process (Immediately Reportable Event Form)
- Adverse event thought to be an allergic reaction to the study vaccine (Immediately Reportable Event Form, unless event meets SAE criteria)
- Any event that, in the opinion of the investigator, precludes further administration of the study vaccine (Immediately Reportable Event Form, unless meets SAE criteria)

### 5.13 Adverse Event Treatment, Follow-up and Outcome

Treatment of any adverse events will be determined by the investigator using his/her best medical judgment and according to current clinical practice guidelines. All applied measures as well as follow-up will be recorded in the appropriate CRF.

Adverse events will be considered resolved when the condition returns to normal or returns to the subject's baseline status as established on Study Day 0, or when the condition has stabilized with the expectation that it will remain chronic.

The investigator will continue follow-up on adverse events, including laboratory abnormalities and solicited adverse events, until the event has resolved, is otherwise satisfactorily explained, or the subject completes the study. If not reported earlier, the outcome of adverse events and solicited adverse events will be determined at the end of the specified post-vaccination adverse event reporting period.

Follow-up for serious adverse events must continue until resolution and the outcome reported to Aeras, even if this extends beyond the serious adverse event reporting period (i.e., after the final study visit). For analysis purposes, the outcome for serious adverse events will be determined on the final study visit.

Outcome of all adverse events will be classified as one of the following:

- Resolved
- Resolved with sequelae
- Ongoing
- Death

If at any time after completion of the serious adverse event reporting period (the final study visit) the investigator becomes aware of a serious adverse event that is suspected by the investigator to be related to the study vaccine, the event must be reported to Aeras.

#### **5.14 Long-term Safety Surveillance**

Subjects enrolled in all Aeras clinical protocols who receive study vaccine will be enrolled into a vaccine development registry protocol for long term surveillance. An informed consent for this protocol will be signed by all enrolled in Aeras clinical product protocols. The primary objective of the registry is to collect cumulative serious adverse event experience and pregnancy outcomes from all clinical trial subjects who have entered an MVA85A/AERAS-485 clinical development study (or other eligible study) until at least two years after marketing authorization has been granted or until the product has been withdrawn from development.

#### **5.15 Subject Diary and Daily Temperature Monitoring**

Parents/guardians of infants who receive study vaccine will receive, and be instructed in, the operation of a daily adverse event diary, a thermometer and a ruler to be used during the specified post-vaccination diary period after vaccine administration. The daily adverse event diary is a source document and will record solicited adverse events, daily thermometer assessments of body temperature, and any other adverse events. During scheduled visits through the specified diary period after study vaccine administration the daily diary will be collected and reviewed by the principal investigator (or designee) at which time any clinical details required for complete understanding of the information recorded will be obtained. Diaries not brought to the scheduled visit should be obtained before adverse event assessment can be performed. Lost diaries will be reconstructed as possible on a new diary booklet by the infant's parents/guardian from memory on the closest scheduled visit and labeled as a reconstructed diary. Adverse events obtained from the diary will be recorded and completely assessed on the adverse event case report form. Body temperatures below 38° C will not be considered fevers.

Any change to an AE recorded by the infant's parents/guardian on the diary card (e.g., the severity level of an event is changed after interviewing the infant's parents/guardian) based on the investigator's evaluation of the event must be explained by notation in source documentation.

## 6 STOPPING RULES

The rules for pausing study vaccine administration by the principal investigator and local medical monitor are in Section 5.1. These rules govern the stopping of further study vaccine administration at any time during the study.

The rules for stopping further enrollment and study vaccine administration by the SMC are below:

- Death in any infant unless the SMC determines it is UNRELATED to MVA85A/AERAS-485
- An anaphylactic reaction to MVA85A/AERAS-485 in any infant
- The occurrence of a serious adverse event unless the SMC determines it is UNRELATED to MVA85A/AERAS-485.

The SMC may permit resumption of study vaccine administration if the study pause was for reasons less severe than those in the SMC stopping rules. The SMC may permit resumption of enrollment if it judges that changes to the study protocol will eliminate or greatly reduce the safety risks specified in the stopping rules. In the absence of study protocol changes, the SMC must follow the SMC study stopping rules.

If a decision to resume study enrollment and study vaccine administration is made the SMC will record their judgment in a memorandum to the study file and notify the sponsor, who will then forward the SMC memorandum to the medical monitors and principal investigators. The clinical site will be allowed to resume activities upon receipt of written notification from the sponsor. The appropriate regulatory authority will be informed in writing if the study is stopped and will be informed in writing of the decision by the SMC to resume or discontinue study activities.

## 7 STATISTICAL CONSIDERATIONS

The planned statistical analyses for this study are outlined below. A detailed statistical analysis plan for preparation of the final study report will be created and made final prior to database lock and before the study is unblinded. A separate analysis plan will be prepared in conjunction with the planned SMC reviews of blinded and unblinded-by-group safety data through Study Day 84 for the safety cohort (Study Group 1) and for the cumulative safety review following completion of the Study Day 84 visit by the 1000th enrollee (see Section 5.1.5), and in conjunction with the interim reviews of accrued TB cases (see Section 7.6); these analyses will be conducted by an unblinded statistician not associated with the study conduct or primary analyses. Separate statistical analysis plans will also be prepared for the gene expression analysis and in conjunction with any summarization of immunogenicity results to be prepared prior to unblinding for preparation of the final study report.

### 7.1 Subject Populations

The safety population will consist of all subjects who received a dose of study vaccine. The per-protocol population for efficacy analyses will consist of all randomized subjects enrolled

in the study who received a dose of study vaccine and had no major protocol deviations. The intent-to-treat population for efficacy analyses will consist of all randomized subjects.

## 7.2 Demographics and Protocol Compliance

Demographic parameters and other baseline characteristics (age [days] at Study Day 0, sex, and race/ethnicity) will be summarized by treatment group, study group, and for all subjects in the safety population. As subject enrollment into individual study groups (cohorts) will be determined based on time of completion of eligibility, any imbalance in baseline characteristics across study groups will be examined.

Listings of randomized subjects who did not receive study vaccine and of subjects with protocol deviations (to be defined in the statistical analysis plan) will be provided.

## 7.3 Efficacy Analyses

Although this study is not designed as an efficacy study, subjects in all study groups will be followed for the development of tuberculosis. Preliminary analyses to evaluate the secondary objective of the efficacy of MVA85A/AERAS-402 will be based on the per-protocol population, as defined in Section 7.1. A secondary analysis will be conducted based on the intent-to-treat population. Clinically applicable definitions of TB disease for this study population will be investigated in this proof-of-concept study.

### 7.3.1 Case definition of tuberculosis

Subjects will be evaluated for the development of TB disease throughout the study based on the procedures described above. Two sets of case definitions for TB will be evaluated in this proof-of-concept study and analyzed in conjunction with the secondary objective of the efficacy of MVA85A/AERAS-485 compared with control. Subjects will be evaluated for the secondary endpoint of TB disease using the clinically relevant TB case definitions below (TB Case Definition Endpoint #1 and #2) as described below. An endpoint related to treatment (TB Case Definition Endpoint #3) will also be analyzed.

The TB case definition endpoints will be applied and analyzed as described below both for subjects investigated for TB in the study case verification ward, and for those subjects who receive a clinical diagnosis of TB disease as part of routine care in other health facilities for whom hospital record review demonstrates that the case meets the study case definition of TB disease given possible limitations in the quality and completeness of all relevant assessments. Handling of missing data during application of the TB Case Definition (e.g., missing chest x-ray data) will be detailed in the statistical analysis plan for the final study report.

#### TB Case Definition Endpoint #1

Any of the following numerical categories

1. Isolation of *M. tuberculosis* from any site.
2. Identification of *M. tuberculosis* by an approved molecular diagnostic technique from any site.
3. Histopathology diagnostic for tuberculosis disease (such as caseating granulomas)

4. Choroidal tubercle diagnosed by an ophthalmologist
5. Miliary pattern on chest X ray in a HIV negative infant
6. Clinical diagnosis of tuberculous meningitis (CSF protein >0.6 g/L and pleocytosis >50/mm^3 with mononuclear cell >50%) with features of basal meningeal enhancement and hydrocephalus on head CT.
7. Vertebral spondylosis
8. A single smear/histology specimen positive for acid fast (or auramine positive) bacilli from a normally sterile body site.
9. One of the following:
  - a) Two acid fast or auramine smears positive each from a separate collection morphologically consistent with mycobacteria from either sputum or gastric aspirate that are not found to be non-tuberculous mycobacteria bacteria on culture , OR
  - b) QuantiFERON conversion from negative or indeterminate to positive, OR
  - c) Tuberculin skin test  $\geq 15$  mm

AND

One of the following compatible radiographic features:

- a) Calcified Ghon focus, OR
- b) Pulmonary cavity, OR
- c) Hilar/mediastinal adenopathy, OR
- d) Pleural effusion, OR
- e) Airspace opacification,

AND

One of the following clinical manifestations:

- a) Cough without improvement for longer than two weeks, OR
- b) Weight loss of at least 10% of body weight for at least 2 months, OR
- c) Failure to thrive (crossing at least one entire major centile band downward) for at least 2 months, where the major centile bands are defined as <97th–90th, <90th–75th, <75th–50th, <50th–25th, <25th–10th, and <10th–3rd weight-for-age centiles\*.

*\*Centers for Disease Control (CDC) Growth Charts (USA), developed by the National Center for Health Statistics in collaboration with the National Center for Chronic Disease Prevention and Health Promotion (2000).*

## **TB Case Definition Endpoint #2**

Any of the following numerical categories

1. Isolation of *M. tuberculosis* from any site.
2. Identification of *M. tuberculosis* by an approved molecular diagnostic technique from any site.
3. Histopathology diagnostic for tuberculosis disease (such as caseating granulomas)
4. Choroidal tubercle diagnosed by an ophthalmologist.
5. Miliary pattern on chest X ray in a HIV negative infant

6. Clinical diagnosis of tuberculous meningitis (CSF protein >0.6 g/L and pleocytosis >50/mm^3 with mononuclear cell >50%) or features of basal meningeal enhancement and hydrocephalus on head CT.
7. Vertebral spondylosis
8. A single smear/histology specimen positive for acid fast (or auramine positive) bacilli from a normally sterile body site.
9. One of the following:
  - a) One acid fast or auramine smear positive morphologically consistent with mycobacteria from either sputum or gastric aspirate that are not found to be non-tuberculous mycobacteria bacteria on culture , OR
  - b) QuantiFERON conversion from negative or indeterminate to positive, OR
  - c) Residence in a household with an AFB smear positive member, OR
  - d) Tuberculin skin test  $\geq 10$  mm

AND

One of the following compatible radiographic features:

- a) calcified Ghon focus, OR
- b) pulmonary cavity, OR
- c) hilar/mediastinal adenopathy, OR
- d) pleural effusion, OR
- e) airspace opacification, OR

AND

One of the following clinical manifestations:

- a) Cough without improvement for longer than two weeks, OR
- b) Weight loss of at least 10% of body weight for at least 2 months, OR
- c) Failure to thrive (crossing at least one entire major centile band downward) for at least 2 months, where the major centile bands are defined as <97th–90th, <90th–75th, <75th–50th, <50th–25th, <25th–10th, and <10th–3rd weight-for-age centiles\*.

*\*Centers for Disease Control (CDC) Growth Charts (USA), developed by the National Center for Health Statistics in collaboration with the National Center for Chronic Disease Prevention and Health Promotion (2000).*

### **TB Case Definition Endpoint #3**

All individuals who are placed on anti-tuberculosis therapy with the intent of treating tuberculosis regardless of whether they have met the other efficacy endpoints

### **7.3.2 Incidence of TB disease**

The number (percentage) of subjects with a diagnosis of TB disease, as defined by TB Case Definition Endpoint #1 in Section 7.3.1, will be used to evaluate the secondary objective of the efficacy of the MVA85A/AERAS-485 vaccine compared to controls in prevention of tuberculosis. The number of subjects with a diagnosis of TB disease will be summarized by treatment group, study cohort, and for all subjects in the per-protocol population. Additional

analyses will be performed based on the intent-to-treat population, and for all subjects who complete the study through end of protocol follow-up. The cumulative person-years incidence of TB and associated 95% confidence intervals during study follow-up will be summarized by treatment group and by study group. Person-time observation will be used to estimate the time at risk of TB and will be calculated based on subject date of last contact with the study minus the date of Study Day 0 vaccination. The incidence of TB disease will be calculated as the number of new cases of TB disease diagnosed during study follow-up, divided by the total person-time of observation. Comparison of the incidence of TB in each treatment group will be performed using relative risk summaries and corresponding 95% confidence intervals, as appropriate, for all subjects in the per-protocol population. Vaccine efficacy for MVA85A/AERAS-485 will be calculated with corresponding 95% confidence interval as  $(1 - \text{relative risk}) \times 100$ . Subjects with multiple TB cases or recurrence will only be counted once in summaries of cumulative incidence.

Time to initial TB diagnosis using Case Definition Endpoint #1 from Study Day 0 in each treatment group will be examined using the Kaplan-Meier estimate of the survival function, and compared using the log-rank test or alternative methodology based on distributional assumptions (to be addressed in the statistical analysis plan). Median time to initial diagnosis and associated 95% CI will be presented by treatment group and for all subjects in the per-protocol population.

The number (percentage) of subjects with a diagnosis of TB disease as defined by TB Case Definition Endpoint #2, and the number (percentage) of subjects meeting either TB Case Definition Endpoint (#1 or #2, Section 7.3.1) will also be summarized by treatment group, study cohort, and for all subjects in the per-protocol population and will be analyzed as described for TB Case Definition Endpoint #1 above. Sensitivity analyses based on the intent-to-treat population will also be performed. Additional analyses will examine differences in number (percentage) of subjects and time to diagnosis for subjects who are excluded from either specific diagnostic criteria categories, and for underlying criteria categorizations (e.g., TST measurement differences).

Exploratory analyses of the number (percentage) of subjects who are placed on anti-tuberculosis therapy during the study for the purpose of treating TB (TB Case Definition #3) will also be performed. Subjects who meet the criteria for this exploratory analysis may or may not also be included in the analyses of the primary TB diagnostic criteria given the endpoint case definitions as defined above. Number (percentage) of subjects placed on anti-TB treatment will be summarized by treatment group, study cohort, and for all subjects, and will be analyzed as described for the TB Case Definition Endpoints #1 or #2, above. Additional sensitivity analyses will be performed to examine differences in number (percentage) of subjects and time to diagnosis for those subjects who are prescribed TB treatment but who do not meet criteria for TB Case Definition Endpoints #1 or #2. Additional exploratory analyses of subjects receiving isoniazid prophylaxis as a result of, e.g., close contact with an adult diagnosed with tuberculosis, will also be performed if warranted by the number of cases. Number (percentage) of subjects receiving isoniazid prophylaxis will be summarized by treatment group and study cohort, with additional analyses performed as described for the TB Case Definition Endpoints #1 or #2, above.

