## 3.3 Assignment to Study Group and Randomization

Infants will be randomized in a 1:1 ratio to MVA85A/AERAS-485 or control within each Study Group using an interactive voice/web response system (IVRS/IWRS). The randomization schedule will be prepared by a statistician who will not be involved with the analysis of the study in order to maintain blinding of the study team.

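### Section 7.3.2 keeps time after a first TB diagnosis in the time-at-risk denominator and promises a median time to diagnosis that cannot be estimated; both are minor and cheap to correct

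*Protocol*

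**What the plan says.** Protocol section 7.3.2 sets the denominator for the incidence rate: person-time, taken as the time at risk of TB, is "calculated based on subject date of last contact with the study minus the date of Study Day 0 vaccination". New cases are then "divided by the total person-time of observation". On repeat disease it says: "Subjects with multiple TB cases or recurrence will only be counted once in summaries of cumulative incidence". The arms are compared by relative risk, and vaccine efficacy is one minus that relative risk.

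The next paragraph of 7.3.2 plans a Kaplan-Meier analysis of time from Study Day 0 to initial TB diagnosis under Endpoint #1, compared by a log-rank test or an alternative left to the statistical analysis plan. It then promises: "Median time to initial diagnosis and associated 95% CI will be presented by treatment group and for all subjects in the per-protocol population".

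Later in 7.3.2, Endpoint #2 and the treatment-based Endpoint #3 are to be analysed in the same way. Section 7.3.1 defines Endpoint #3 as "All individuals who are placed on anti-tuberculosis therapy with the intent of treating tuberculosis", whether or not the other definitions are met.

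**The concern.** An infant who has been diagnosed can no longer contribute a new countable case, so later follow-up is not time at risk of the event in the numerator. That follow-up does accrue: section 3.5 keeps vaccinated infants on the visit schedule unless consent is withdrawn, and section 3.5.6 provides for readmission to the case verification ward after a completed course of TB treatment. Section 7.3.2 is therefore inconsistent with itself, because its Kaplan-Meier clock ends at initial diagnosis and its incidence-rate clock, for the same endpoint, does not. Rates come out too low, and more so in the arm with more cases. If the vaccine works, the rate ratio is pulled towards 1.

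The median is a separate defect. A Kaplan-Meier median exists only if the curve falls to 50%, and TB at the assumed rate comes nowhere near that. A promised output would be empty.

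**Working it through.** **Inputs.** From section 7.6: control cumulative incidence 3% over 18 months, a 60% reduction, 1392 infants per arm, 7.5% lost over 18 months, and a two-sided log-rank test at 0.05 with 90% power. From section 2.2: follow-up of 15 to 39 months. From appendix Table 3 (endpoint case distribution, a results table used here only as a cross-check): Endpoint #1 in 39/1395 placebo and 32/1399 vaccine infants; Endpoint #2 in 3.8% overall; Endpoint #3 in 12.7% and 14.0%, 13.4% overall.

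**The plan's own figure.** With hazard ratio 0.4 and exponential dropout of 7.5% over 18 months, 1392 per arm gives about 56.4 expected events. Freedman's formula gives power Φ(√56.4 × 0.6/1.4 − 1.96) = Φ(1.26) = 89.6%. The stated 90% reproduces, so these planning inputs are used below.

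**Person-time, Endpoint #1.** Assume a constant hazard λ and a common follow-up T.
- The written rule estimates F/T, where F = 1 − exp(−λT). The correct rate is λ, so written/correct = F/(λT).
- Control: λT = −ln(0.97) × T/18, with T in months. Vaccine: 0.4 times that.
- Efficacy under the written rule is 1 − F(vaccine)/F(control).

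| T (months) | λT control | F control | Control rate understated | F vaccine | Efficacy as written (true 60%) |
|---|---|---|---|---|---|
| 18 | 0.03046 | 0.03000 | 1.5% | 0.01211 | 59.6% |
| 24 | 0.04061 | 0.03980 | 2.0% | 0.01611 | 59.5% |
| 39 | 0.06600 | 0.06386 | 3.2% | 0.02605 | 59.2% |

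At the 15-month minimum the control understatement is 1.3%. The vaccine rate is understated by 0.6%, 0.8% and 1.3% in the three rows.

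**Cross-check on the Table 3 counts**, taking equal follow-up per infant as one unit:
- Written rule: 1 − (32/1399)/(39/1395) = 18.2%.
- Diagnosis at mid-follow-up on average: 1 − (32/1383)/(39/1375.5) = 18.4%.
- Extreme case, every diagnosis on day 0: 1 − (32/1367)/(39/1356) = 18.6%.

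**Endpoints #2 and #3.** With common follow-up (about 24 months, say), F/(λT) depends only on the cumulative proportion, so the exact length drops out.
- Endpoint #2 at 3.8%: 0.038/0.03874 = 0.981, an understatement of 1.9%.
- Endpoint #3 at 13.4%: 0.134/0.1439 = 0.931, an understatement of about 7%.
- Endpoint #3 ratio, vaccine to control: correct −ln(0.860)/−ln(0.873) = 0.1508/0.1358 = 1.11; written 0.140/0.127 = 1.10.

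**Median.**
- Control cumulative incidence at the 39-month maximum: 1 − 0.97^(39/18) = 6.4%. The survival curve stays above 0.93.
- Implied control median: ln 2/λ = 0.6931/(0.03046/18) = about 410 months, or 34 years.
- Even Endpoint #3, the broadest, reaches only 13.4%.

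**The case against.** The strongest reply is that almost nothing turns on this. Efficacy is a secondary objective, and section 7.3 says the study was not designed as an efficacy study. Section 7.3.2 opens by saying that the number and percentage of infants with TB will be used to evaluate efficacy. That fits a risk ratio, which uses no person-time, so efficacy is touched only if relative risk means the rate ratio. For Endpoint #3, which is exploratory, both rates shrink almost equally. The median is one descriptive line that would be reported as not reached, and the planned Kaplan-Meier curve already contains the cumulative incidence.

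All of this stands as to size. It does not make the text right. The relative-risk sentence says it compares the incidence of TB, which the section has by then defined as cases over person-time, so the rate-ratio reading is at least open. Nor can the unseen statistical analysis plan be presumed to settle it: the deferral in 7.3.2 covers the choice between the log-rank test and an alternative, whereas the person-time rule and the median are stated outright.

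A reader might also infer that the log-rank test is wrongly unstratified, since section 3.3 says: "Infants will be randomized in a 1:1 ratio to MVA85A/AERAS-485 or control within each Study Group". The protocol does not support that. It specifies neither a stratified nor an unstratified test and leaves the method to the statistical analysis plan. An unstratified test is also valid after 1:1 allocation within groups. In simulation (assumed entry over 21 months with Study Group 1 first, and up to a twofold hazard difference between groups), type I error was 5.0–5.4% unstratified against 4.8–5.3% stratified. Power at a hazard ratio of 0.6 agreed within 0.5 points.

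**Conclusion.** The point holds and is minor. The time-at-risk definition in 7.3.2 is wrong as written for every endpoint it serves, and the promised median with its confidence interval cannot be produced. On the protocol's planning rate, the Endpoint #1 control rate is understated by about 1.5% to 3.2%, and a true efficacy of 60% reads 59.2% to 59.6% if relative risk is the rate ratio. Endpoint #3 rates are about 7% low, with the ratio moving only from about 1.11 to 1.10. These sizes assume a constant hazard and a common follow-up time. The Kaplan-Meier and log-rank analyses of time to initial diagnosis are unaffected.

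Two stronger readings should not be drawn. The efficacy conclusion is not materially biased: the shift is under one percentage point. Nor do randomised but unvaccinated infants in the intent-to-treat set lack a start date. Sections 3.1 and 3.2.3.1 make Study Day 0 the day of randomisation, so the reference to vaccination in the person-time rule is an editorial matter.

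**What to change.** In section 7.3.2, count person-time from Study Day 0, the day of randomisation, to the earliest of the first diagnosis qualifying for the endpoint being analysed, last contact, or end of study. Apply this separately to Endpoints #1, #2 and #3. In the same edit, state whether relative risk means the rate ratio or the risk ratio.

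Replace the median with Kaplan-Meier cumulative incidence by arm and the between-arm difference, each with a 95% confidence interval, at fixed times such as 12, 18 and 24 months.

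The cost is wording and programming. No new data, visits or infants are needed, and the power calculation does not change.
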